## Abstract

**Background:**

Functional constipation (FC) in children is a common gastrointestinal disorder with a worldwide-pooled prevalence of 9.5%. Complaints include infrequent bowel movements, painful defecation due to hard and/or large stools, faecal incontinence, and abdominal pain. Prebiotic oligosaccharides have been shown to relieve constipation symptoms in young adults and elderly. However, sufficient evidence is lacking linking additional prebiotic intake to improve symptoms in children with FC. We hypothesise that prebiotic oligosaccharides are able to relieve symptoms of constipation in young children as well.

**Methods:**

In the present randomised, double-blind, placebo-controlled, multi-centre study, we will study the effects of two prebiotic oligosaccharides in comparison to placebo on constipation symptoms in children of 1–5 years (12 to 72 months) of age diagnosed with FC according to the Rome IV criteria for functional gastrointestinal disorders. The primary outcome measure will be change in stool consistency. Secondary outcomes include stool frequency and stool consistency in a number of cases (%). Tertiary outcomes include among others painful defecation, use of rescue medication, and quality of life. In addition, the impact on gut microbiome outcomes such as faecal microbiota composition and metabolites will be investigated. Participants start with a run-in period, after which they will receive supplements delivered in tins with scoops for 8 weeks, containing one of the two prebiotic oligosaccharides or placebo, followed by a 4-week wash-out period.

**Discussion:**

This randomised double-blind, placebo-controlled multi-centre study will investigate the effectiveness of prebiotic oligosaccharides in children aged 1–5 years with FC.

**Trial registration:**

ClinicalTrials.gov NCT04282551. Registered on 24 February 2020.

**Supplementary Information:**

The online version contains supplementary material available at 10.1186/s13063-024-08050-8.

## Introduction

### Background and rationale

Functional constipation (FC) in children is a common gastrointestinal (GI) disorder with a worldwide prevalence ranging from 0.7 to 29.6%, with a pooled prevalence of 9.5% [1, 2]. Only a minority of patients with FC, both children and adults, seek healthcare [3]. However, it is estimated that up to 25% of visits to a paediatric gastroenterologist are due to FC [4]. Complaints include infrequent bowel movement, painful defecation due to hard and/or large stools, faecal incontinence, and abdominal pain [4]. FC is a clinical diagnosis; the evaluation primarily consists of a thorough medical history and is based on the paediatric diagnostic Rome IV criteria for functional GI disorders (Table 1) [5–7]. Although the condition is rarely life-threatening, it strongly impairs quality of life. The impairment in health-related quality of life is comparable with conditions such as diabetes, rheumatoid arthritis, and chronic allergies [8].

**Table 1 Tab1:** Rome IV criteria for functional constipation

< 4 years of age [5]	Developmental age of > 4 years [6]
Must include 1 month of at least 2 of the following in infants up to 4 years of age: 1. 2 or fewer defecations per week 2. History of excessive stool retention 3. History of painful or hard bowel movements 4. History of large-diameter stools 5. Presence of a large faecal mass in the rectum In toilet-trained children, the following additional criteria may be used: 6. At least 1 episode/week of incontinence after the acquisition of toileting skills 7. History of large-diameter stools that may obstruct the toilet	Must include 2 or more of the following occurring at least once per week for a minimum of 1 month with insufficient criteria for a diagnosis of irritable bowel syndrome 1. 2 or fewer defecations in the toilet per week in a child of a developmental age of at least 4 years 2. At least 1 episode of faecal incontinence per week 3. History of retentive posturing or excessive volitional stool retention 4. History of painful or hard bowel movements 5. Presence of a large faecal mass in the rectum 6. History of large-diameter stools that can obstruct the toilet After appropriate evaluation, the symptoms cannot be fully explained by another medical condition

The aetiology of FC is still incompletely understood but is likely to be multifactorial. Some factors in children which have been described are withholding behaviour, psychosocial factors such as stressful life events or behavioural problems, behavioural disorders, parental child-rearing attitudes, low fibre intake, and gut microbiota composition [4, 7, 9]. Standard treatment of FC in children includes demystification, education, toilet training, and laxative treatment with, among others, polyethylene glycol (PEG) [10, 11]. Laxatives such as PEG are safe, but adherence to laxatives is low, and except for the use of PEG, little is known about the long-term effects of chronic laxative use [4, 12]. This may explain why 36.4% of parents of children with FC seek help in the form of food supplements and complementary or alternative medicine [13]. One such alternative might be prebiotic oligosaccharides. Galacto-oligosaccharides (GOS) and chicory fructo-oligosaccharides (FOS; synonym oligofructose) are oligosaccharides that belong to the category of prebiotics. Prebiotics are defined by the International Scientific Association for Pro- and Prebiotics (ISAPP) as “a substrate that is selectively utilised by the host microorganisms conferring a health benefit” [14]. GOS and FOS have been shown to selectively stimulate certain gut microbial species, mostly bifidobacteria and lactobacilli, and have demonstrated health benefits, and consequently are endorsed as prebiotics by ISAPP [15–17].

Prebiotic oligosaccharides are of interest due to several factors: (1) low fibre intake has been associated with FC, and oligosaccharides are also considered dietary fibres; (2) fermentation of oligosaccharides is known to increase the abundance of gut microbiota thereby increasing faecal bulk; (3) oligosaccharide-derived microbial fermentation products such as short chain fatty acids (SCFAs) have been described to give energy to colonic epithelial cells and may generate an osmotic effect in the gut, which can increase the water content of faeces, leading to softening of stools; and finally (4), these prebiotics are known to modify the composition of the gut microbiota which may indirectly affect bowel habit via gut-brain signalling. These hypotheses are supported by the fact that prebiotic oligosaccharides have shown stool-softening effects in trials in healthy infants and children with infant, follow-on and young child formulas supplemented with prebiotics [16–25].

In addition, some trials showed improvement in stool consistency in children with FC after the consumption of prebiotic oligosaccharides. However, evidence linking oligosaccharide and/or fibre intake to improved symptoms in children with FC is rather weak [11, 26–30]. This is not only due to the low number of studies, but also the small sample size of studies, overall poor quality of methods used, and incomplete reporting of results. Therefore a large-scale, well-executed study is needed to investigate if the consumption of GOS or FOS can result in improved bowel habits and modify the gut microbiota in young children with FC.

### Objectives

We hypothesise that consumption of GOS or chicory FOS will result in softer stools, improvement of some other constipation-related symptoms and modifications of the gut microbiota in comparison to a placebo. Therefore the aim of the study is to investigate the effect of GOS or FOS versus a placebo on bowel habits and microbiota in children with FC aged 1–5 years.

### Trial design

This is a randomised, double-blind, placebo-controlled, multi-centre trial with three arms: GOS, chicory FOS and placebo, in which GOS will be compared to placebo and FOS will be compared to placebo in a superiority framework.

## Methods

This study (named ‘Inside study’) is a double-blind, randomised, placebo-controlled, multi-centre trial. We aim to enrol 198 children, aged between 1 and 5 years, with FC according to the Rome IV criteria (Table 1).

### Study setting

This study is coordinated by Wageningen University & Research, Laboratory of Microbiology. The study is conducted in The Netherlands. Patients from the outpatient clinics in the Emma Children’s Hospital, Amsterdam, Amsterdam University Medical Centres Amsterdam (AUMC), DeKinderKliniek Almere, Spaarne Gasthuis Haarlem, Haaglanden MC Den Haag, Rijnstate ziekenhuis Arnhem and Maasstad ziekenhuis Rotterdam, will be recruited by their treating paediatric gastroenterologist. More participating centres may follow.

### Eligibility criteria

#### Participant screening

Eligible patients will be contacted by researchers of Wageningen University & Research to answer questions the patients might have and to verify whether or not they are willing to participate, to avoid an undesirable dependency situation with the treating paediatric gastroenterologist.

#### Inclusion criteria

In order to be eligible to participate in this study, a subject must meet all of the following criteria, as considered by a medical doctor:Written informed consent obtained from parents or guardians of children meeting the eligibility criteria and those willing to comply with the requirements of the study.Aged 1–5 years (12 to 72 months at the day of inclusion).Children that meet/fulfil the Rome IV criteria for FC.

#### Exclusion criteria

Any of the following criteria will result in exclusion of a potential subject from this study:Children who suffer from any GI complaints other than FC, known structural GI abnormalities, or previous GI surgery.Any condition that would make it unsafe for the child to participate. This can include developmental delays associated with musculoskeletal or neurologic conditions affecting the GI tract. Children with an underlying cause of defecation disorder (for example, Hirschsprung’s disease, spina bifida occulta, cystic fibrosis, or GI malformations).Children with clinically significant cardiac, vascular, liver, pulmonary, psychiatric disorders, severe renal insufficiency, human immunodeficiency virus, acquired immunodeficiency syndrome, hepatitis B or C or known abnormalities of haematology, urinalysis, or blood biochemistry, as checked by the inclusion questionnaire.Children who are lactose intolerant, or who are self-perceived lactose intolerant or for whom it is expected that low doses of lactose could lead to GI symptoms.Children who are allergic to cow’s milk or fish.Use of antibiotics or other medicines or food supplements, and breast milk-feeding, which can influence defecation and gut microbiota 4 weeks prior to the study run-in period and during the study itself.The use of infant formula, follow-on formula, young child formula in the previous week prior to the study run-in period and during the study itself.Children on other supplements/medication that could affect bowel function, including e.g. fibre supplements, and pre-, pro- and synbiotics (excluding rescue medication) for the past 4 weeks and during the study itself.Children that participate in another clinical trial.

#### Informed consent procedure

Informed consent will be obtained by the researchers or treating paediatric gastroenterologist either at one of the outpatient clinics or at a home visit before the start of the study, see Additional file 1.

### Interventions

After the run-in period, participants will receive either Vivinal^®^ GOS powder (FrieslandCampina, Amersfoort, The Netherlands), Frutalose^®^ OFP chicory oligofructose (Sensus, Roosendaal, The Netherlands) or placebo (maltodextrin) supplements in tins with scoops. The substances are approved food grade ingredients, they have been previously used in other clinical trials and are used in several food products. All supplements were similarly powders light in colour with a pleasant taste. All supplements are in identical tins with scoops and were produced according to good manufacturing practice standards. One scoop (8.5 mL size) should be consumed per day, with half a dose in the first 3 days to avoid any potential side effects such as flatulence caused by intestinal fermentation of FOS or GOS. The product should preferably be dissolved in warm or cold drinks such as milk or semi-solid products such as yoghurt. The intervention product will be consumed for 8 weeks (Fig. 1).

**Fig. 1 Fig1:**
[figure not shown]
Study protocol flow. Visit 1 is at day = 1, call 1 at day = 7, call 2 at day = 63 (end of 9 weeks), visit 2 at day = 91 (end of 14 weeks), which will be a home visit to pick up samples and leftover product. During visits 1 and 2, anthropometrics (weight, height and head circumference) will be measured. *Diary includes filling out stool consistency and frequency and compliance of taking the study product. FFQ, food frequency questionnaire; FOS, chicory fructo-oligosaccharides; GOS, galacto-oligosaccharides; QOL, quality of life questionnaire

Rescue medication should be used if the participant does not have a bowel movement for 3 consecutive days, being either microlax 5 mL, sodium picosulphate pearls (1 droplet per 5 kg body mass) or glycerine (glycerol) suppositories (1 g, 2 g or 4 g). These types of laxatives were chosen as they have a mode of action based on provoking peristalsis, and thereby are expected to have minimal effect on gut microbiota composition [31]. This is in contrast to (fermentable) osmotic laxatives such as lactulose or PEG, which were found to influence gut microbiota composition [32].

Despite that rescue medication may be required, the child will still remain in the study. Each use of rescue medication needs to be reported in the diary to differentiate between spontaneous bowel movements and those related to rescue medication use. To further exclude an influence of escape medication on gut microbiota outcomes, a stool sample should only be collected after a spontaneous defecation and at least 3 days after the last use of escape medication.

### Outcomes

#### Primary objective

The main study parameter is the change in stool consistency, measured by the validated Dutch-modified Bristol Stool Form Scale (mBSFS) [33]. This will be the mean difference in stool consistency of GOS versus placebo and FOS versus placebo at all time points (week 1, 3, 6, 9 and 13) and from baseline to week 9.

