### Participant timeline

After randomisation, patients will enter a 1-week run-in period, after which they will either receive GOS, FOS or a placebo for 8 weeks. Lastly, a 4-week run-out period is in place to investigate whether a possible effect lasts or not. The flow of the study protocol is presented in Fig. 1.

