### Statistical methods

#### Statistical analysis for primary, secondary and tertiary outcomes

Data will be presented as mean ± standard deviation (SD) if normally distributed, or median (interquartile range) when skewed. To test associations between continuous parameters, multiple linear regression will be used. For categorical or dichotomous outcomes, generalised estimation equations or mixed models for repeated measures will be used. Data will be tested for confounding or effect mediators, and confounding factors will be added to the regression. In case of missing data, they will be imputed by multiple imputation or other appropriate methods. All data will be assessed using the statistical program R (The R Foundation for Statistical Computing, Vienna, Austria). A *p*-value of < 0.05 will be considered statistically significant. In order to prevent p-hacking, a false discovery rate correction will be applied for microbiota analyses, of which a *q*-value of < 0.1 is regarded statistically significant. Either GOS or chicory FOS versus the placebo will be analysed for all parameters.

A variety of in-house R-scripts and the Phyloseq package will be used for microbiota composition analyses. To assess variation in microbiota composition, 16S rRNA gene sequence data will be tested for differences between groups in α-diversity (phylogenetic diversity; the number of observed species and inverted Simpson’s for evenness and richness) and β-diversity (Bray–Curtis dissimilarity distances, weighted and unweighted unifrac distances; methods for constrained and unconstrained ordinations; significance of variations by e.g. adonis test). Principal response curves will be used to check the development of the gut microbiota over time. Moreover, an area under the curve assessment for microbiota will be done. For 16S rRNA gene sequence data, a qPCR-based abundance of specific taxa selected based on sequence data and SCFA’s (multiple) linear regression will be used to test the predictive power of the model.

Changes in stool pH, results of the TAPQOL and changes in stool characteristics will be tested by a repeated measure analysis. Differences between timepoints will be assessed using mixed models.

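### The primary outcome lists up to 12 contrasts, including a pre-product week and an off-product week, and none is named as the one that decides the trial

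*Protocol article*

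**What the plan says.** The Primary objective section gives the main parameter as change in stool consistency on the modified Bristol scale. It then spells this out as a "mean difference in stool consistency of GOS versus placebo and FOS versus placebo at all time points (week 1, 3, 6, 9 and 13"). The same sentence adds a sixth item, the change up to week 9. The abstract names change in stool consistency as primary and gives no week.

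The Participant timeline fixes what the weeks mean: "After randomisation, patients will enter a 1-week run-in period, after which they will either receive GOS, FOS or a placebo for 8 weeks". Week 1 is therefore run-in and weeks 2 to 9 are on product. Weeks 10 to 13 are described thus: "a 4-week run-out period is in place to investigate whether a possible effect lasts or not".

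The Statistical methods section says that "changes in stool characteristics will be tested by a repeated measure analysis" and that mixed models will assess differences between time points. A p-value "of < 0.05 will be considered statistically significant". The only multiplicity provision is that "a false discovery rate correction will be applied for microbiota analyses". The Sample size section treats one two-group comparison at α = 0.05 with 80% power and names no week.

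**The concern.** A primary outcome should tell the reader which result makes the trial positive. Here six quantities per product share primary status with no order among them.

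Two of the listed weeks cannot show an on-product effect. At week 1 no child has received product, so any difference between randomised arms is chance. At week 13 the children have been off product for four weeks, and by the protocol's own account that period asks whether an effect lasts.

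At stake is the meaning of a positive primary result. If the arms differ at week 3 but not at week 9, or only at week 13, the text does not say whether the trial succeeded. If the best of the listed contrasts could be claimed, the 5% error rate used for the sample size no longer describes the trial.

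**Working it through.** **Count.** 2 products × (5 weeks + 1 change from baseline to week 9) = 12 contrasts, or 6 per product.

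**The plan's own figure.** Inputs from the Sample size section are D = 0.35, SD = 0.65 and factor 7.9. Then n = 2 × 7.9 × (0.65/0.35)² = 54.49 per group, which matches the stated 54.5. Next, 54.5 × 1.2 = 65.4, rounded up to 66 per arm, and 3 × 66 = 198, also as stated. This calculation covers one two-group contrast and makes no allowance for two products or several weeks. After 20% drop-out, 66 × 0.8 = 52.8 children per arm remain evaluable.

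**Chance of at least one false positive.** The protocol states no such figure, so this was simulated (300,000 replicates per setting) under no effect of either product:

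- Three equal arms share one placebo group, so the two products' test statistics at the same week correlate 0.5.
- The within-child correlation ρ between weeks is not given. It is assumed equal for all pairs of weeks and varied from 0 to 0.9.
- The statistic for change to week 9 is (z₉ − z₁)/√(2(1 − ρ)).
- Each test is two-sided at 0.05, and any one significant result counts as positive.

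| ρ | 6 contrasts, one product | 12 contrasts, both products | 10 contrasts (week 1 left out), both products |
|---|---|---|---|
| 0 | 24% | 40% | 36% |
| 0.3 | 23% | 38% | 35% |
| 0.5 | 21% | 35% | 32% |
| 0.7 | 18–19% | 31% | 29% |
| 0.9 | 14% | 25% | 24% |

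If correlation instead decays with time (0.80, 0.90 or 0.95 per week), the 12-contrast figures are 36%, 32% and 28%. Twelve independent tests would give 1 − 0.95¹² = 46%. That is too high here, because the contrasts are correlated.

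**Change-from-week-1 reading.** If week 1 is only the baseline and the contrasts are changes to weeks 3, 6, 9 and 13, there are 2 × 4 = 8 tests. With equal correlations, two changes from the same baseline have correlation (1 − ρ)/(2(1 − ρ)) = 0.5 whatever ρ is. The result is about 16% per product and 27% across both, at every ρ.

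**One contrast per product.** Baseline to week 9 alone gives 5% per product and 9% across both.

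**Power at the planned size.** This takes the protocol's SD as that of the chosen contrast. The standard error is 0.65 × √(2/52.8) = 0.1265, and 0.35/0.1265 = 2.767.

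- At two-sided 0.05: Φ(2.767 − 1.960) = 79%.
- At two-sided 0.025: Φ(2.767 − 2.241) = 70%.

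**The case against.** The best defence is that the protocol never says that 12 tests will be run, or that one significant contrast makes the trial positive. The main parameter is introduced in the singular. The listed weeks are also the diary weeks, so they may be just the measurement schedule for the repeated measures analysis planned in Statistical methods. Week 1 would naturally be the baseline of that model. The Trial design section compares each product with placebo as its own question, so pooling error across the two is optional. Finally, a statistical analysis plan may exist and may settle testing order and adjustment.

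Much of this stands. A reader might infer that the trial carries a one-in-three chance of a false positive. The documents do not support that as a flat statement. It pools two separately posed questions, assumes a middling within-child correlation that the protocol does not give, and relies on an any-one-wins rule that the protocol does not write. A reader might also take the listed weeks as one five-week average, with the effect diluted by weeks 1 and 13. Nothing in the text says the weeks are averaged, so no loss of power should be claimed on that ground.

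The core survives. A repeated measures model yields many contrasts, and the protocol names neither one of them nor an overall test as decisive. Nor is this mere silence left to an analysis plan: the protocol itself gives primary status to all five weeks plus the change, and states a correction only for microbiota.

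**Conclusion.** The primary outcome is badly fixed. Up to 12 contrasts carry primary status without a deciding one, and the list includes a pre-product week and an off-product week. That follows from the text without any assumption.

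The size is conditional. If any single contrast below 0.05 could be claimed as a positive primary result, the false-positive chance is about 14–24% per product and 25–40% across both, for an assumed within-child correlation of 0 to 0.9, equal between weeks. On the change-from-week-1 reading it is about 16% and 27%. Against these stand 5% and 9% with one week-9 contrast per product. Even on the readings kindest to the plan, the per-product figure is well above the 5% on which the sample size rests.

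**What to change.** Before unblinding, amend the Primary objective so that each product has one primary contrast: the between-arm difference in stool consistency from baseline to week 9. This is already in the text. It can be estimated from the planned repeated measures model, with week 1 used only as baseline. Make weeks 3 and 6 secondary as time course, and week 13 secondary as persistence.

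Then state one of two things: that each product is a separate 5% claim, or which adjustment applies across the two. If 0.025 is used for each, disclose that power is about 70% with 52.8 evaluable children per arm, against 79% at 0.05.

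The cost is wording only, with no new data. The protocol plans no interim analyses and describes recruitment as not yet complete, so on its own account the change can be made blind. Any analysis plan should carry the same definition.
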